### Data collection

Data collection took place over a period of 4–8 weeks per center (except for one center, where the data collection took 12 weeks) from May 2015 until January 2016. During data collection, a research assistant was stationed at the PHCC. The research assistant identified and recruited the eligible participants and gave oral and written information on the study. All participants were also asked to provide informed consent for the study, including linking records to registers during follow-up (Fig. 1).

**Fig. 1 Fig1:**
[figure not shown]
The procedure of datacollection and follow-ups, TIDAS in New Ways

### Intervention group

The intervention consisted of the following components: GPs’ brief training in the use of the WSQ, participants’ completion of the WSQ, GP feedback at consultation and finding suitable preventive measures. The WSQ consists of 21 main questions grouped into four categories [28]. Two of the categories pertain to perceived stress due to *indistinct organization and conflicts* and perceived stress due to *individual demands and commitment*. Each of these two categories contains seven items. Response options are given on a four-point ordinal scale: ‘Not at all stressful’, ‘Less stressful’, ‘Stressful’, and ‘Very stressful’. The other two categories pertain to *influence at work* and *work interference with leisure time,* and contain four and three items, respectively, with response options given on a four-point ordinal scale: ‘Yes, always’, ‘Yes, rather often’, ‘No, seldom’ and ‘No, never’. The reliability and face validity of the WSQ has been tested and found to be good [28].

Before the GP consultation, each participant filled in the WSQ and questions on background characteristics, which took around 15 min. The research assistant computed the WSQ and handed over the result to the GP before consultation. At the patient–GP consultation, the GPs were instructed to give feedback to the participant by communicating the results of the WSQ, and discussing possible measures, such as referrals to PHCC’s specialists or to the participant’s occupational healthcare (Fig. 1).

Directly after each patient–GP consultation, the GP filled in a questionnaire concerning their adherence to the instructions.

### Control group

Control participants received TAU, i.e. an ordinary patient–GP consultation. The GP had no information on whether the patient was a study participant. After the GP consultation, the participant completed the WSQ and answered questions on background characteristics (Fig. 1).

### Baseline assessments

Self-reported baseline characteristics were collected by questionnaire on gender (female, male), age (years), country of birth (Nordic, other), educational level (compulsory schooling, secondary school education, university or higher education), occupation, employer (private, public, self-employed), employment status (permanent, temporary, self-employed), and the reason for consulting the PHCC (mental and/or physical health complaints).

### Follow-up outcome measurements

All registered data will be collected one year after last inclusion, i.e. January 2017.

#### Primary outcome

The number of registered sick leave days (i.e. 14 days or more) and number of absence periods during the 12 months after inclusion covered by sickness benefit will be obtained from the Swedish social insurance agency’s Micro Database for Analyzing Social insurance (MiDAS) as well as data on full- and part-time sick leave and sickness and activity compensation.

#### Secondary outcome measurements

Short term sick leave (<14 days) and present work status are collected at 3, 6, and 12 months by telephone or email follow-up.

Healthcare measures will be obtained from the Vega database, which covers data on hospital and primary health care patients in the Västra Götaland region of Sweden. Data concerning diagnoses, number of visits, referrals, and content of consultations and measures during the 12 months following inclusion.

Data on prescribed medications will be obtained from the Swedish Prescribed Drug Register, a national population-based register established in 2005, which contains information on all purchases of prescribed medications in pharmacies [36]. Data concerning the name and amount of purchased medication, date dispensed, and dosage instructions during the 12 months following inclusion.

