### Aims and hypothesis

The overall aim of this randomized controlled trial (RCT) is to evaluate whether systematic use of the WSQ, combined with feedback at consultation, can serve as a method for health care professionals in primary health care centers (PHCCs) to prevent or reduce sick leave due to work-related stress during a 12-month follow-up period. The preventive intervention will be compared versus treatment as usual (TAU). The aim is also to evaluate whether there are differences between the intervention group and the control group in healthcare measures and the prescribed medications at follow-up. In a process evaluation, the systematic use of the WSQ combined with feedback at consultation is examined.

The hypothesis of this RCT is that patients who answer the WSQ, when combined with feedback at GP consultation, will have fewer sick leave days during the year after intervention compared with those who receive TAU.

This paper presents the study design, the procedure, the outcome measurements, the allocation and the baseline characteristics of the study population. The project is still ongoing, with follow-up data to be collected and analyzes to be done. The RCT was designed in accordance with CONSORT recommendations [34].

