### Procedure

Prior to the intervention period, the research team visited the participating PHCC and presented the study procedure. The control GPs were instructed to carry on as usual with their consultations. The intervention GPs received a brief training for the intervention, which included knowledge on the relationship between psychosocial factors at work, stress, health and sickness absence. GPs also received instructions on how to use, operationalize and interpret the WSQ, and on how to give feedback to the participants and refer patients at risk. Both oral and written information on the services of the primary health care specialists and occupational healthcare was presented to the GPs.

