### Masking (blinding)

Neither participants nor the GP were blinded to allocation in the RCT because of the nature of the intervention. All participants were given information on the study and signed consent forms before the patient–GP consultations. However, the control GPs were not informed when a patient for consultation was a study participant, and the controls filled in the questionnaires after consultation.

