Fortunately, we reached our target sample size for participating patients. Also, the fact that few sociodemographic differences were identified between the groups was an advantage. The intervention participants were somewhat older and had a higher rate of musculoskeletal complaints as reasons for consultation. The rates of patients declining and being excluded from participation were low, and no differences concerning gender and age were observed. A limitation is that we did not collect data on non-participation patients’ reasons for consultation or reasons to decline participation because of ethical considerations.

The advantages of randomizing at the GP level were considered as twofold: the risk for variations in sociodemographic and socioeconomic factors between participating patients in intervention and controls were reduced, and engaging the whole PHCC to recruit both to intervention and control groups led to more participants attending in earlier studies [44]. The disadvantage of randomizing at the GP level was the risk for contamination, because the GPs might discuss the study procedure with each other. Because the inclusion period was short, and the intervention was brief and imbedded in ordinary daily practice, the contamination risk was considered rather low.

A strength of this project is that both qualitative and quantitative methods were used in the process evaluation. The focus group methodology involves group discussions and is distinguished from other qualitative group interviews by the explicit use of group interaction to collect data on a specific research topic. Communication between the participating focus group members is decisive for the outcome and the group process encourages the participants to clarify not only what they think, but also how and why they think in a certain way [38, 45]. An experienced group leader was chosen to moderate the sessions because the role of the group leader is essential in creating an open and friendly atmosphere that makes participants feel free to express their views [45]. In addition to using the questionnaires on GPs’ readiness and feasibility in the process evaluation, they will be analyzed in relation to the outcome variables.

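### The 12-month referral and measures outcomes appear to include the index consultation, so a difference between arms can reflect delivery of the intervention rather than healthcare at follow-up

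*Protocol article*

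**What the plan says.** All references are to the protocol article.

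- **Window and items** (Secondary outcome measurements): "Data concerning diagnoses, number of visits, referrals, and content of consultations and measures during the 12 months following inclusion". The source is named just before: "Healthcare measures will be obtained from the Vega database, which covers data on hospital and primary health care patients".
- **Aim** (Aims and hypothesis): to look for "differences between the intervention group and the control group in healthcare measures and the prescribed medications at follow-up". No direction is given. The stated hypothesis concerns sick leave days only.
- **Order of events** (Masking): "All participants were given information on the study and signed consent forms before the patient–GP consultations". This holds in both arms.
- **Intervention at the index consultation**: under Procedure, intervention GPs were instructed "on how to give feedback to the participants and refer patients at risk". Under Intervention group, the consultation includes "discussing possible measures, such as referrals to PHCC’s specialists or to the participant’s occupational healthcare", and finding suitable preventive measures is listed as a component of the intervention. Control GPs give an ordinary consultation.
- **Contamination** (Discussion): "Because the inclusion period was short, and the intervention was brief and imbedded in ordinary daily practice, the contamination risk was considered rather low".

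**The concern.** Referrals and measures appear twice in the design. They are part of what intervention GPs were trained and told to do at the index consultation, and they are also secondary outcomes counted from inclusion. Since consent precedes the consultation, the outcome window seems to open before the intervention is delivered. Nothing shown separates what was done at that consultation from what happened afterwards.

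Interpretation is at stake, not the validity of the randomised comparison. If the intervention arm has more referrals or measures over 12 months, the unsplit figure does not say whether GPs acted on their instructions on day one or whether patients' later healthcare differed. The stated aim is about follow-up, so readers are likely to take the second meaning.

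The index-date record is also useful in its own right. The adherence questionnaires and the process evaluation cover intervention GPs only. Of the data sources described, the register is the one that could show in both arms what was done at the consultation.

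**Working it through.** The article states no referral rate, visit rate or expected difference for the healthcare outcomes, so there is no figure of its own to reproduce here. The sample size of 135 per group concerns sick leave days and does not bear on this point.

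**Inputs from the article:** 132 intervention and 139 control participants; two-sided significance level 0.05; one index consultation per participant in each arm.

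**Assumed inputs, for illustration only:** probability of referral at the index consultation p = 10% in controls and 20% or 30% in the intervention arm; probability of a later referral q = 10–40%, equal in both arms and independent of index referral; patients treated as independent, ignoring clustering by GP.

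**Step 1: any referral over 12 months.** For one arm, P = 1 − (1 − p)(1 − q). The gap between arms is therefore (p_int − p_con)(1 − q).

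- Smallest: (0.20 − 0.10)(1 − 0.40) = 0.06.
- Largest: (0.30 − 0.10)(1 − 0.10) = 0.18.

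**Step 2: chance of p < 0.05.** Power = Φ[(gap − 1.96·SE0)/SE1], where SE0 uses the pooled proportion and SE1 the separate proportions. For the largest gap (37% v 19%):

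- pooled proportion = (0.37×132 + 0.19×139)/271 = 0.278
- SE0 = √[0.278×0.722×(1/132 + 1/139)] = 0.0544
- SE1 = √(0.37×0.63/132 + 0.19×0.81/139) = 0.0536
- (0.18 − 1.96×0.0544)/0.0536 = 1.37, so power is 91%.

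| Later referral, both arms | Index 10% v 20%: control v intervention at 12 months | Gap (points) | Chance of p < 0.05 | Index 10% v 30%: control v intervention at 12 months | Gap (points) | Chance of p < 0.05 |
|---|---|---|---|---|---|---|
| 10% | 19% v 28% | 9 | 41.7% | 19% v 37% | 18 | 91.4% |
| 20% | 28% v 36% | 8 | 29.2% | 28% v 44% | 16 | 78.7% |
| 30% | 37% v 44% | 7 | 21.5% | 37% v 51% | 14 | 64.2% |
| 40% | 46% v 52% | 6 | 16.5% | 46% v 58% | 12 | 50.7% |

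**Step 3: the same scenarios counted from the day after the index consultation.** Both arms have probability q, so the gap is q − q = 0 in every row. The whole 6–18 points comes from the index consultation.

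**Step 4: number of visits.** The index visit adds 1 per participant in each arm, so it contributes 1 − 1 = 0 to the difference. The point is confined to referrals and to the content of consultations and measures.

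**The case against.** The strongest reply has four parts.

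1. **The comparison is valid as it stands.** The aim asks only whether the arms differ. A total counted from inclusion is a proper intention-to-treat contrast, and more referrals would be a genuine effect of offering the questionnaire with feedback. This stands, and it is why the total should be kept. It does not make the total a measure of healthcare after the consultation.

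2. **The start day is not stated.** The article does not say whether extraction begins on the day of inclusion or the day after, and a full protocol or SAP, not shown here, may settle it. This stands in part. That the index consultation is counted is an inference, though the plain one given when consent is signed. If the window already starts the next day, the referral outcome is sound and only the index-date table remains to be added.

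3. **A difference is not guaranteed.** A reader might infer that one must appear by construction. The article does not support that: GPs were to discuss possible measures, with referral as an example, so whether referrals rose is an empirical question. An index-day calculation also overstates the size. At 30% v 10%, index referral alone gives z = 0.20/√(0.3×0.7/132 + 0.1×0.9/139) = 0.20/0.0473 = 4.2, but the planned window is 12 months and later referrals dilute the gap, as the table shows.

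4. **No visits are meant to be saved.** A reader might also infer that visits created by referral cancel against visits the intervention should prevent, so that equal counts hide a benefit. No passage says that the intervention is meant to reduce visits, so that argument tests a claim the trial does not make.

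Nor does the article say that the register items will be collapsed into one 12-month sum. The index-date data are not lost; they are only not set apart.

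**Conclusion.** The point holds in a limited form and is minor. On a plain reading, the referral and measures outcomes include the consultation at which the intervention was delivered, so a 12-month difference in them can arise from delivery alone. It is not by itself evidence of different healthcare at follow-up.

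Under the assumed rates, the gap from delivery alone is 6–18 points, with about a 17% to 91% chance of reaching p < 0.05. These figures rest on assumed referral rates, equal and independent later referral, and no clustering. They show that the choice of window can matter, not that it will. The index visit does not shift visit counts, and the primary outcome of registered sick leave is unaffected.

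**What to change.** 1. State whether the index consultation falls inside the outcome window.
2. Keep the total from inclusion as the intention-to-treat contrast.
3. Report referrals and measures on the index date by arm, labelled as delivery and contrast data. This also informs the low-contamination statement in the Discussion, though only in part: similar rates in the two arms could mean contamination or weak adherence.
4. Report referrals, measures and visits from the day after the index consultation, for all randomised participants, as the follow-up healthcare outcome. Read it beside the index-date table, since an index referral may replace a later one.
5. Do not base claims on visit counts that leave out visits following an index referral. That selects on an event after randomisation whose frequency may differ by arm, and could itself create a difference. Such visits may be described, no more.

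**Cost:** a sentence in the analysis plan, a date split of register data already planned, and one more table. **Limit:** the register is described as covering hospital and primary care, so referrals to occupational healthcare, one of the two named targets, may not be fully captured. The table should say so.

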### Statistical analysis

The analyses will follow the intention-to-treat principle [37]. Per protocol analyses will be conducted to examine if deviations from the protocol have caused bias. Both descriptive and analytic statistics will be used to compare the intervention group and the control group. Analysis will be adjusted for gender and other possible confounders. Sub-group analyses will be done with regard to gender, and if possible given the number of participants, age and diagnostic groups. Non-parametric statistics will be used when ordinal data are analyzed. Otherwise, parametric statistics will be used [37].

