### Study design and recruitment

This study was designed as a two-armed RCT for early identification of people at risk for sick leave due to work-related stress consulting PHCCs. The recruitment of PHCCs took place from May 2015 to November 2015. Out of the Västra Götaland region’s 200 PHCCs, 51 public and private PHCCs located in rural and urban areas in and around Gothenburg were identified and consecutively invited to participate. In all, seven PHCCs (four public and three private) participated. The PHCCs were economically compensated for each participant recruited.

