### Randomization

GPs and residents who worked in the clinic at participating PHCCs at least 50% of the time were randomized to either the intervention or the control group. The names of all GPs at the participating PHCC were written on slips of paper that were folded and then mixed in a non-transparent bowl. Colleagues that were not involved in the RCT drew the names one at a time, and the names were alternately included in the intervention or the control group.

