### Allocation and baseline characteristics

In total, 66 GPs were randomized to either the intervention group or to the control group. One GP declined participation and two GPs were excluded because of not having the target group at consultation. The intervention group (systematic use of the WSQ and feedback during patient–GP-consulting) consisted of *n* = 29 GPs and the control group (TAU) of *n* = 34 GPs (Fig. 2).

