**Fig. 2 Fig2:**
[figure not shown]
Flow chart of enrolment, allocation and baseline, TIDAS in New Ways

During the inclusion period, 301 non-sick-listed employed women and men aged 18 to 64 years who sought care at the seven participating PHCCs in the Västra Götaland region and fulfilled the inclusion criteria were asked to participate in the study. Of these, 20 eligible patients (7%) declined to participate. A total of 10 patients (3%) were excluded because they left the PHCC before being asked to fill in the questionnaires. No statistically significant differences in responses by participant age or gender were found. The final study population consisted of 271 participants (Fig. 2), of which 132 belonged to the intervention group and 139 to the control group.

The mean age was 46 years (standard deviation = 12) in the intervention group and 43 years (standard deviation = 11) in the control group, with a larger proportion in the age group 51–64 among intervention participants. Also, a larger proportion in the intervention group was consulting the PHCC for musculoskeletal reasons. Otherwise, there were no statistically significant differences between the groups in terms of baseline characteristics concerning sociodemographic factors and reasons for consulting the PHCC (Table 1).

**Table 1 Tab1:** Characteristics of participants in the intervention and control groups, *n* = 271, TIDAS in New Ways

	Intervention *n* = 132	Control *n* = 139
	n^a^ (%)	n^a^ (%)
Gender		
Female	88 (67)	97 (70)
Age categories		
19–30 years	21 (16)	26 (19)
31–50 years	58 (44)	76 (54)
51–64 years	53 (40)	37 (27)^c^
Birthplace		
Nordic countries	122 (93)	125 (90)
Other	9 (7)	14 (10)
Educational level		
Compulsory schooling	13 (10)	15 (11)
Secondary school	61 (46)	59 (42)
University or higher	57 (44)	65 (47)
Occupational class		
Skilled/unskilled manual	49 (37)	58 (42)
Medium/low non-manual	60 (46)	56 (41)
High-level non-manual	23 (17)	24 (17)
Employer		
Private	61 (46)	68 (49)
Public	66 (50)	61 (44)
Self-employed	5 (4)	9 (7)
Reason for consultation^b^		
Mental or behavioral	75 (57)	69 (50)
Musculoskeletal	62 (47)	44 (32)^c^
Gastrointestinal	26 (20)	28 (20)
Cardiovascular	16 (12)	16 (16)
Other	29 (22)	27 (19)

^a^Dispersed numbers of participants are owing to internal

missing data

^b^Multiple responses were optional

^c^Statistically significant differences (tested with the 95% CI for difference in proportion)

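### GPs were randomised, but the article names no GP cluster or centre stratum and points to a patient-level analysis; intervals would be too narrow if outcomes correlate within GP

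*Protocol article*

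**What the plan says.** **Unit of allocation.** The Randomization section states that "GPs and residents who worked in the clinic at participating PHCCs at least 50% of the time were randomized". On the draw it says "The names of all GPs at the participating PHCC were written on slips of paper", with names then assigned alternately to the two arms. This reads as a separate draw in each centre. The Discussion fits that reading, since it describes whole centres recruiting to both arms. Study design and recruitment gives the number of centres: "In all, seven PHCCs (four public and three private) participated".

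**Numbers.** Allocation and baseline characteristics reports "In total, 66 GPs were randomized to either the intervention group or to the control group". After one refusal and two exclusions, the intervention group "consisted of *n* = 29 GPs and the control group (TAU) of *n* = 34 GPs". The final 271 patients are those "of which 132 belonged to the intervention group and 139 to the control group".

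**Analysis.** Statistical analysis says "Both descriptive and analytic statistics will be used to compare the intervention group and the control group". It adds intention-to-treat and per-protocol analyses, adjustment for gender and other unspecified confounders, subgroups, and a choice between non-parametric methods (ordinal data) and parametric methods (all else). No GP effect, PHCC effect or clustered variance is named.

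**Other places that bear on the unit of analysis.**
- Sample size asks for 135 participants per group and gives no ICC, cluster size or design effect.
- Table 1, footnote c, describes the baseline comparison as "Statistically significant differences (tested with the 95% CI for difference in proportion", applied to patient counts.
- The Discussion weighs GP-level randomisation and names contamination as its disadvantage. Correlation between patients of the same GP is not mentioned.

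**The concern.** The trial is cluster-randomised by design: no patient was randomised, and 271 patients sit within at most 63 GPs in seven centres. The GP delivers the intervention through training, feedback and choice of measures, and the process evaluation records each GP's adherence. Some GP-level variation in effect and outcome is therefore plausible. It is most plausible for the secondary outcomes that reflect practice, such as referrals and prescriptions.

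If patients of the same GP resemble one another, a comparison that treats the 271 patients as independent has standard errors that are too small, intervals that are too narrow and a type I error above the stated 5%. PHCC matters as well. When allocation is balanced within centres, leaving centre out keeps between-centre variation in the error term, and the analysis no longer reflects the design. The primary comparison of sick leave and all secondary between-arm comparisons are exposed.

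**Working it through.** **1. The plan's own sample size.** The 135 per group cannot be reproduced uniquely, because no control rate, mean or SD is given. A formula for independent patients can reach it. For two proportions (two-sided 5%, 80% power, no continuity correction), 34% against 19% gives

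n = [1.96·√(2·0.265·0.735) + 0.8416·√(0.34·0.66 + 0.19·0.81)]² / 0.15² = 134.7, so 135.

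The rates are my assumption. The figure is compatible with a patient-level calculation, and the section states no allowance for clustering.

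**2. Patients per GP** (Allocation and baseline characteristics). Intervention 132/29 = 4.55; control 139/34 = 4.09; overall m = 271/63 = 4.30. This assumes that all 63 retained GPs contributed patients, which the article does not say.

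**3. Design effect and true test size.** The article gives neither the ICC nor the coefficient of variation (CV) of patients per GP, so both are assumed.

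- DE = 1 + [(1 + CV²)·m − 1]·ICC
- True size of a nominal 5% patient-level test = 2·[1 − Φ(1.96/√DE)]
- Shortfall in interval width relative to the correct width = 1 − 1/√DE

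Example: CV 0 and ICC 0.05 give DE = 1 + 3.30·0.05 = 1.165. Then 1.96/√1.165 = 1.816, and the size is 6.9%.

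| ICC | CV | DE | True size | Interval too narrow by |
|---|---|---|---|---|
| 0.01 | 0 | 1.03 | 5.4% | 2% |
| 0.05 | 0 | 1.17 | 6.9% | 7% |
| 0.10 | 0 | 1.33 | 8.9% | 13% |
| 0.01 | 0.7 | 1.05 | 5.6% | 3% |
| 0.05 | 0.7 | 1.27 | 8.2% | 11% |
| 0.10 | 0.7 | 1.54 | 11.4% | 19% |

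**4. What the table leaves out.** It covers GP clustering only. With allocation within PHCC, differences between centres largely cancel from the arm comparison. An analysis that omits centre still counts them as error, which makes its standard errors too large. That offsets the inflation above by an amount the article does not allow one to compute.

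**5. Do the Table 1 flags reveal the method?** Simple binomial 95% intervals from the printed counts:

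- Age 51–64: 53/132 − 37/139 = 13.5 points, SE 5.68, interval 2.4 to 24.7.
- Musculoskeletal: 62/132 − 44/139 = 15.3 points, SE 5.87, interval 3.8 to 26.8.

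Both exclude zero, matching the flags. Widening by √1.33 gives 0.7 to 26.4 and 2.1 to 28.6, so both still exclude zero. The age flag is lost only when DE exceeds (13.53/11.13)² = 1.48, which happens in just one of the six scenarios (1.54). The flags cannot tell clustered from unclustered intervals.

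**The case against.** The strongest reply is that the article is silent rather than wrong. It names no test or model. A GP random-intercept model is parametric, PHCC could be one of the adjustment variables, and a condensed article may leave the model to an analysis plan that is not shown. This stands in part: the article does not say that patients are treated as independent, and silence in one section would not be a finding. But the patient is the working unit in the sample size, in the Table 1 tests and in the discussion of what GP-level allocation costs. The mismatch with the unit of randomisation lies in the text itself.

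Three stronger readings are tempting and are not supported:

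- *Table 1 proves that independence was assumed.* Footnote c's wording suggests a simple method, but the flags survive design effects up to about 1.48. They also concern a baseline description, not the outcome analysis.
- *The GP seen at inclusion controls the outcome by certifying sick leave.* Study context says only that a certificate is required from day 8. Nothing says that the same GP issues certificates over the next 12 months.
- *The p-values will be wrong by the amounts tabulated.* The ICC and CV are assumed and the PHCC strata pull the other way. The double-digit test size needs both ICC 0.10 and CV 0.7.

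**Conclusion.** The point holds as a mismatch: allocation is by GP, apparently within PHCC, while everything the article says about sizing, testing and analysis points to patients, with no GP or PHCC term. Whether a patient-level analysis would do harm depends on a within-GP correlation that the article does not give. From GP clustering alone, over an assumed ICC of 0.01 to 0.10, the design effect is 1.03 to 1.33 with equal numbers per GP and 1.05 to 1.54 at CV 0.7. The inflation is small at the low end and material at the high end. The net error, once the omitted PHCC strata are counted, is not known in size. Because the ICC cannot be judged until it is estimated, the analysis should follow the allocation and not rely on the effect being small.

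**What to change.** In Statistical analysis, state that every between-arm comparison uses a model with GP as the cluster and PHCC as a fixed stratum. The model can be a GP random intercept, or GEE with robust standard errors corrected for a small number of clusters. Base the reference degrees of freedom on the number of GPs who contributed patients. A permutation test that re-allocates GPs within PHCC is an acceptable alternative. Report the GP-level ICC for the primary outcome. If an analysis plan already specifies this, one sentence in the article pointing to it is enough.

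The cost is wording and, usually, slightly wider intervals. No new data are needed: each patient's GP and PHCC should be known from the allocation, and the article says that the analyses are still to be done.
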